### Outcome Measures

#### Overview

The following measures of emotion regulation (primary outcome), mood symptoms (secondary outcome), and loneliness (secondary outcome) will be administered pre- and postintervention via Qualtrics (Silver Lake Technology Management, L.L.C.).

#### Primary Outcome: Emotion Regulation

The Emotion Regulation Questionnaire is a widely used measure with subscales assessing 2 styles of emotion regulation: cognitive reappraisal and expressive suppression. It has been translated and validated for use in Hong Kong (Cronbach α=0.80-0.83) [53]. A child and adolescent version of the scale has also been translated into Chinese [54]. Given that the primary focus of the Tuned In program is to encourage the outward expression of emotion through music, it is anticipated that changes will be observed in expressive suppression scores, but not necessarily in cognitive reappraisal scores, following the program.The Difficulties in Emotion Regulation Scale (DERS) is a more comprehensive measure that assesses emotional awareness, emotional acceptance, impulse control, and emotion regulation strategies among both adolescents and adults. This scale has also been validated for use with Chinese participants (Cronbach α=0.68-0.89) [55]. Given its comprehensive nature, the DERS is considered the primary outcome measure in this study.To measure confidence in managing emotions, items from the program evaluation tool used by Dingle and Carter [27], which explicitly asks participants to rate their self-confidence in managing both positive and negative emotions, will also be included.

#### Secondary Outcomes: Mood Symptoms And Loneliness

The 21-item Depression Anxiety Stress Scale (DASS-21), which has been used with Chinese participants [56], will be used to measure mood symptoms. Recent research has demonstrated the scale’s validity for assessing emotional distress among young people in Hong Kong [57].The Hong Kong version of the 6-item De Jong Gierveld Loneliness Scale (Cronbach α=0.76) [58] will be used to assess loneliness.

### Additional Measure

We will use the Music USE (MUSE) Questionnaire [59] to assess each participant’s typical music listening habits, including whether they play a musical instrument and if they have received formal musical training. This scale was successfully used in a study involving 1318 adolescents in Hong Kong [34], making it a valuable tool for describing participants’ engagement with music.

For demographic information such as gender and socioeconomic status collected in the survey, tests will also be conducted across the 2 conditions to examine whether the results differ.

The effect of the intervention on reducing anhedonia will also be explored using the Chinese version of the Snaith-Hamilton Pleasure Scale [60]. Data collected from this scale will be used for future outcome analysis.

The Tuned In program’s acceptability among Hong Kong adolescents will be examined using a combination of quantitative and qualitative approaches. Satisfaction ratings will be collected from participants using a 7-point Likert scale. With “strongly disagree” at 1 point and “strongly agree” at 7 points, the ratings will capture the extent to which participants agree with the positive statements. The questions will address the perceived usefulness of the program, the level of interest in the program, the likelihood of recommending the program to other adolescents, and the likelihood of continuing to use music as an emotion regulation strategy in the future [25]. The aforementioned areas of investigation regarding the project’s acceptability are framed into 4 separate rating questions, all of which are included in the postintervention survey. The quantitative questions are provided in Multimedia Appendix 3.

In addition, we will include open-ended qualitative questions to gather feedback from participants on their experiences with the program and to collect suggestions for improvements for a future RCT. Written responses are expected from participants. As feasibility indicators, we will also record the recruitment rate and dropout rate for this trial. The qualitative questions are incorporated into the postintervention survey, to be completed by participants at the end of the final session.

To explore participants’ continued use of music for emotion regulation after the program, invitations to qualitative interviews will be sent at the 1-month follow-up. All participants who received the intervention will be invited. Open-ended and probing questions will be used to gather descriptive data on participants’ views of the program and their music listening habits. Data saturation is expected to be reached by the conclusion of the project. Please refer to Multimedia Appendix 3 for the interview and postintervention survey questions.

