### Study Design

The study adopts a waitlist RCT design. Participants are randomly assigned to either the intervention group, who will receive the program immediately, or the waitlist control group, who will receive the intervention after a 4-week waiting period. The main assessment time points are pre- and postintervention for the intervention group, and baseline and postwaiting period for the control group. Additionally, the control group will be invited to complete an optional postintervention survey following their participation, which will be used for secondary data analysis. The postintervention surveys for both groups will contain identical items to ensure comparability. It is also planned that all participants who complete the intervention will be invited to take part in an optional qualitative interview to gain deeper insights into their experiences using the strategies taught in the program.

Given the project’s strong emphasis on psychoeducation, participants’ application of the strategies taught serves as an indicator of the program’s acceptability. Qualitative inquiry offers valuable insights into the extent to which participants have internalized and consolidated the healthy coping strategies introduced during the intervention. This approach enables exploratory interpretations of the project’s outcomes and helps uncover the nuanced, individualized experiences of participants. Therefore, qualitative research is considered appropriate to capture the subjective and personal dimensions of the intervention’s impact.

Online delivery was chosen in response to the prevailing pandemic conditions at the time. This decision not only aligned with the original program design but also helped overcome geographical barriers. By eliminating distance as a constraint, the online format significantly enhanced the accessibility of the program. While this mode of delivery presented challenges—such as difficulty in maintaining participants’ attention and limited nonverbal communication—it also expanded the potential of digital platforms to support mental health through digital expressive arts and peer support [47]. Moreover, the web-based design increased the mobility and flexibility of the intervention [48]. Previous studies have shown that online group interventions can be effective in reducing mental health symptoms such as depression [43,48], and Draper and Dingle [49] found that virtual groups were effective in addressing psychological needs.

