By the end of the last session, participants will be invited to complete the postquestionnaire. Individuals who complete both the prequestionnaire and postquestionnaire will receive a reimbursement of HK $200 (US $25.77) in cash. Reimbursement will be provided in person, and participants will be required to sign a receipt for record-keeping purposes. The intervention for the control group will be delivered after the final session of the experimental group and upon completion of the postquestionnaire by its participants. A flowchart outlining the project has been included in Multimedia Appendix 2.

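### Acceptability ratings and written feedback are planned only for the end of the last session, so they describe completers and are likely, though not certain, to be more favourable than those of everyone who started

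*Protocol article*

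**What the plan says.** Additional Measure sets out how acceptability is measured. Four satisfaction items on a 7-point agreement scale cover usefulness, interest, recommending the programme and continued use of music, "all of which are included in the postintervention survey". Written feedback is collected in the same survey, "to be completed by participants at the end of the final session". Description of the Intervention gives the same timing: "By the end of the last session, participants will be invited to complete the postquestionnaire". Payment depends on the questionnaires: "Individuals who complete both the prequestionnaire and postquestionnaire will receive a reimbursement of HK $200".

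For the waitlist arm, Study Design says that "the control group will be invited to complete an optional postintervention survey following their participation". Its main second assessment comes after the waiting period, before those participants have had the programme.

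The sections differ on interviews. Study Design says that "all participants who complete the intervention will be invited to take part in an optional qualitative interview". Additional Measure, describing the invitations sent at one month, says: "All participants who received the intervention will be invited".

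Additional Measure also records the recruitment and dropout rates as feasibility indicators. Study Design treats participants' use of the taught strategies as a further sign of acceptability.

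**The concern.** Acceptability is a stated question of this pilot, and the written comments are meant to improve a later trial. Someone who attends one or two sessions and leaves has experience of the programme that bears directly on that question. The survey as timed does not ask that person anything. If such people liked the programme less, the average rating is too favourable as a description of those who began it, and the suggestions come only from those who stayed.

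The interview is the only other described source of participants' views. Under the Study Design wording it too is closed to people who stop early. Under the Additional Measure wording it is open to them, but it is optional, comes a month later and is described as collecting descriptive answers, not the four ratings.

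No later analysis can supply ratings that were never collected, so this has to be settled in the data collection plan.

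**Working it through.** **The plan's own figures.** The document gives no numerical target or assumption for acceptability. The nearest figures are in Sample Size Calculation and Contingency Plan:

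- Required number: 98, from a partial eta squared of 0.076. With f² = 0.076/(1 − 0.076) and a noncentral F test on 1 and N − 2 degrees of freedom at two-sided 5%, N = 98 gives 80.3% power. The 98 therefore reproduces if 80% power was intended; the article does not state the power.
- Attrition: 15%.
- Recruitment: about 50 adolescents + 65 young adults = 115. After 15% loss, 115 × 0.85 = 97.75, or about 98.
- Adolescents retained after the intervention: at least 30.

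**Numbers without a rating.** At 15%, 115 × 0.15 = 17.25, so about 17 people. Among adolescents, at the retention floor, 50 − 30 = 20, and 20/50 = 40%.

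**Shift in the mean.** Let d be the share of starters who give no rating, C the mean of those who rate and D the mean that the others would have given. The mean for all starters is (1 − d)C + dD. The reported mean exceeds it by

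C − [(1 − d)C + dD] = d(C − D).

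The gap C − D is not in the document and is assumed here:

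| Assumed gap (points) | d = 0.15 | d = 0.40 (adolescent worst case) |
|---|---|---|
| 0 | 0 | 0 |
| 1 | 0.15 | 0.40 |
| 2 | 0.30 | 0.80 |

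**The same on a percentage scale.** Suppose 85% of completers agree with an item (assumed) and between 0% and 85% of leavers would have agreed. The figure for all starters then lies between 0.85 × 0.85 = 72% and 85% when d = 0.15, and between 0.85 × 0.60 = 51% and 85% when d = 0.40.

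**What these figures assume.** The 15% is treated as loss among people who started. Sample Size Calculation speaks of losses both after and before the start, so the share of starters may be smaller. Every completer is assumed to respond. In the waitlist arm that is doubtful, because the relevant survey is optional. Non-response there would raise d, but the article gives no response rate from which to size it.

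**The case against.** Four objections carry weight.

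- **Direction.** The article gives no reasons for dropout and no ratings from people who left. Those who leave because of timetables, schoolwork or technical trouble might rate the programme as highly as those who stay. The gap could be zero, so a reader who infers that the result is definitely biased upward goes beyond the document. This stands, and the range above starts at zero for that reason.
- **The adolescent figure.** The 40% comes from a floor of at least 30 retained, set against a recruitment target at randomisation. Some of that loss may be people who never start and do not belong among starters, and both figures pool the two arms. It is a worst case, not an expectation. This stands.
- **Visibility.** The dropout rate is recorded, so the loss will be seen. This stands in part: a rate does not show what leavers thought or why they left, and the article does not tie the ratings to it.
- **Condensed detail.** A journal article may leave out late survey links. Payment depends on completing both questionnaires, not on attending the last session. So the stronger claim, that anyone who misses the last session cannot give a rating, is an inference from the timing statements. What remains is that every statement of timing points to the end of the last session and no other route is described.

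A reader might also infer that the decision to run a larger trial turns on these ratings. The article sets no threshold or progression rule for acceptability, so that is not supported. End-of-programme ratings are a common pilot choice, and here they are an additional measure, not a primary or secondary outcome.

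**Conclusion.** The point holds in a limited form. As written, people who start and stop early give no ratings and no written suggestions. Waitlist participants are asked about the programme they received only in an optional survey. The two statements on interview eligibility conflict. The ratings therefore describe responding completers.

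They are likely, but not shown, to be more favourable than the ratings of all starters. At the planned 15% attrition the overstatement is 0 to 0.30 points on the 7-point scale for an assumed gap of 0 to 2 points. Among adolescents it could reach 0.80 points with a 2-point gap, but only at the 40% worst case. Every figure rests on the assumed gap and on treating the stated attrition as loss among starters.

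The change is worth making because it is cheap and the missing ratings cannot be recovered afterwards.

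**What to change.** 1. Send the four ratings, the written feedback questions and an optional question on reasons for leaving through the existing Qualtrics survey. Send them to everyone in either arm who attended at least one session and has not declined further contact, whether or not they attended the last session. State a fixed response window, for example 7 days.
2. Reconcile Study Design with Additional Measure so that interviews are offered to all who received any session.
3. Report the ratings with the number of respondents out of the number who started, beside the dropout rate, and limit the conclusion to respondents.

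**Cost.** A few messages through the WhatsApp channel already in use, and some extra reimbursements. If all of the roughly 17 people lost at 15% attrition replied and were paid, this would be 17 × HK$200 = HK$3,400. Reported satisfaction may be lower. Some people who left will not reply, so selection is reduced but not removed.

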### Data Analysis

For the main outcome evaluation measures, mixed measures ANOVAs will be performed. The between-participants factor is group (intervention vs control), and the within-participants factor is time (pre- vs postintervention). Before the main analyses, independent samples *t* tests (2-tailed, paired) will be conducted on the baseline demographic variables to identify any significant differences between the 2 groups. Any variables that show statistically significant differences will be included as covariates in the subsequent main analyses. It is expected that the treatment group will demonstrate improved emotion regulation and reduced mood symptoms and loneliness following the music intervention, compared with the control group. A medium effect size is anticipated for the significant group × time interaction effect.

All verbal and written feedback will be analyzed using thematic analysis [61]. The qualitative analysis software NVivo (QSR International) will be used to assist with the process. Content analysis will be conducted following the transcription and coding of the data.

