### Sample Size Calculation

Dingle and Fay [6] found a medium effect size (η^2^_p_=0.076) for improved emotion regulation after the music intervention with young adults, compared with the control group. Based on this medium effect size, at least 98 participants are needed to detect a significant group × time interaction effect (*P*<.05). However, based on previous trials, some dropout is expected after the intervention has commenced. The estimated attrition rate is 15%. Besides, considering that partnerships with middle schools have only recently begun to develop, while many university students have already expressed interest in committing to the project, we expect to recruit more university participants. Therefore, we aim to recruit over 100 participants for the randomization stage, including around 50 adolescents and 65 young adults, to account for possible dropouts before the intervention begins.

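### The group × time test on pre and post scores is valid but less efficient than adjusting for the baseline score, which the plan collects and does not name as a covariate

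*Protocol article*

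**What the plan says.** The Primary Outcome section settles the measure: "the DERS is considered the primary outcome measure in this study". Study Design gives one assessment before and one after: "The main assessment time points are pre- and postintervention for the intervention group, and baseline and postwaiting period for the control group".

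Data Analysis fixes the method: "For the main outcome evaluation measures, mixed measures ANOVAs will be performed". It then defines the model: "The between-participants factor is group (intervention vs control), and the within-participants factor is time (pre- vs postintervention"). The effect of interest there is the group × time interaction, and Sample Size Calculation sizes the trial on the same test: "at least 98 participants are needed to detect a significant group × time interaction effect (*P*<.05").

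On covariates, Data Analysis says that t tests "will be conducted on the baseline demographic variables to identify any significant differences between the 2 groups", and then: "Any variables that show statistically significant differences will be included as covariates in the subsequent main analyses". The baseline score of the outcome is not named as a covariate anywhere in the article.

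**The concern.** In a 2 × 2 mixed ANOVA, the interaction F test is algebraically the square of the two-sample t test on post minus pre. That test does use the baseline, but with a slope fixed at 1. When the pre-post correlation is below 1 and the two variances are similar, the true slope is below 1 and the change score subtracts too much of the baseline.

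Two things follow. First, precision is lost on the DERS and on every secondary scale measured before and after. Second, if one arm starts worse by chance, regression to the mean makes it appear to improve more, and the change score passes part of that imbalance into the estimated effect. Screening demographic variables does not deal with imbalance in the outcome score itself.

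The article chooses this method explicitly and builds its sample size on it, so it is not a detail left open for a later analysis plan.

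**Working it through.** **Inputs**
- Effect size: Sample Size Calculation says an earlier trial "found a medium effect size (η^2^_p_=0.076) for improved emotion regulation after the music intervention with young adults".
- N = 98 and significance level 0.05: same section.
- Power: not stated; 80% is assumed.
- Allocation: taken as 1:1, because block randomization is meant to balance the groups.
- Pre-post correlation ρ and the ratio k = post SD / pre SD: not given, so ranges are shown.

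**Step 1: reproduce 98**
- f² = 0.076 / (1 − 0.076) = 0.08225, so f = 0.2868, and the standardised difference on change scores is d = 2f = 0.574.
- Noncentral F test with 1 and N − 2 degrees of freedom, λ = N·f², two-sided 0.05. At N = 98, λ = 8.06 and power is 80.3%; 98 is the smallest N that reaches 80%.
- Alternatives do not fit: 85% power needs 112, 90% needs 130, and a one-sided test needs 76. A repeated-measures formula that treats f as a raw-score effect gives 50 (ρ = 0) or 26 (ρ = 0.5).
- The stated 98 is therefore a change-score comparison at 80% power.

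**Step 2: variance ratio with equal pre and post variances σ²**
- Change score: 2σ²(1 − ρ).
- Post score adjusted for baseline: σ²(1 − ρ²).
- Ratio: (1 − ρ²) / [2(1 − ρ)] = (1 + ρ)/2, below 1 for every ρ < 1.

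**Step 3: power with the same treatment effect**

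Use λ = N·f² / [(1 + ρ)/2] with N − 3 degrees of freedom.

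| ρ | Variance ratio | Power at 98, adjusted | N for 80%, adjusted |
|---|---|---|---|
| 0.5 | 0.75 | 90.1% | 74 |
| 0.6 | 0.80 | 88.1% | 79 |
| 0.7 | 0.85 | 86.2% | 84 |
| 0.8 | 0.90 | 84.2% | 88 |
| 0.9 | 0.95 | 82.2% | 93 |
| As planned | 1 | 80.3% | 98 |

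A simulation with 49 per arm and 8000 runs per setting agrees. Power was 80.2% (change score) against 90.0% (adjusted) at ρ = 0.5, and 80.5% against 85.8% at ρ = 0.7. Type I error was 4.6% to 5.3% for both tests.

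**Step 4: unequal variances**
- General ratio: k²(1 − ρ²) / (1 + k² − 2ρk).
- k = 1.2, ρ = 0.7: 1.44 × 0.51 / (2.44 − 1.68) = 0.7344 / 0.76 = 0.966; power 81.6%.
- k = 1.2, ρ = 0.8: 0.5184 / 0.52 = 0.997; power 80.4%.
- k = 1.25, ρ = 0.8: 0.5625 / 0.5625 = 1; no gain. Here the true slope ρk equals 1, which is exactly what the change score assumes.

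**Step 5: chance imbalance**

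Suppose the arms differ at baseline by δ through chance. With equal variances the expected post-score difference due to δ is ρδ, but the change score subtracts δ. Its estimate is then off by −(1 − ρ)δ for that imbalance, for example −0.3δ at ρ = 0.7. Baseline adjustment subtracts the estimated slope times δ.

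**The case against.** The strongest reply is that nothing here is an error. The analysis and the sample size agree with each other, the interaction test is unbiased under randomization and holds its type I error, and the article describes a seed-funded pilot. All of that stands: this is a loss of efficiency, not a fault in validity. It does not make the choice one of taste, because the alternative uses the same data, costs one degree of freedom and is, in large samples, never less precise.

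The size of the gain is also open to challenge. Neither ρ nor the variance ratio is in the article, and Step 4 shows that the gain can disappear. That stands, so the figures are a range under a stated assumption.

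Three stronger readings are tempting and not supported:
- *The plan throws the baseline away.* It does not; the change score uses the baseline with a slope of 1.
- *Selecting on a GHQ-12 score of 3 or above biases the comparison through regression to the mean.* Selection comes before randomization and acts on both arms alike, so average regression cancels between them. It is also on a different scale from the DERS. Only chance imbalance between arms matters.
- *Only 85 participants will complete, so power is already about 74%.* That takes the target as exactly 100. The article itemises about 50 + 65 = 115, and 115 × 0.85 = 97.75, essentially 98.

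**Conclusion.** The point holds as a matter of efficiency. The planned test is valid and correctly sized, but it gives up precision on the primary and secondary scales and over-corrects chance imbalance in the outcome at baseline. At 98 completers, adjusting for baseline would raise power from about 80% to between 82% (ρ = 0.9) and 90% (ρ = 0.5). This assumes 80% planned power, equal pre and post variances and independent participants. The gain shrinks toward nothing as ρ nears 1, or as the product of ρ and the SD ratio nears 1.

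One caveat applies to both analyses: each assumes that baseline answers are unaffected by knowledge of allocation. Randomization and Blinding has participants told their allocation after randomization, typically two weeks before the intervention starts. Description of the Intervention has the baseline survey completed at the introductory session. Read together, these leave the assumption in doubt, and baseline adjustment does not cure it.

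**What to change.** In Data Analysis, prespecify the primary analysis as a linear regression of post-intervention (post-waiting) DERS on arm and baseline DERS, reporting the adjusted mean difference with its 95% confidence interval. Use the same form for each secondary scale with its own baseline score. Keep the group × time ANOVA as a sensitivity analysis. The baseline score should enter as a fixed, named covariate and not depend on a baseline significance test.

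The cost is a change of wording and one error degree of freedom; no new data are needed. The sample size can stay at 98, with the gain treated as a margin because ρ is unknown. Separately, the article should state whether the baseline survey is completed before or after participants learn their allocation. If it is after, moving it would be a change of procedure, not of wording.

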### Material and Personnel Preparation

The group sessions are cofacilitated by 2 individuals: a research assistant with a background in a mental health–related discipline and a registered music therapist. The research assistant takes the lead in delivering the psychoeducational content, while the music therapist facilitates the musical experiential activities and supports group discussions. Both facilitators employ techniques such as encouraging participants to be “good group members” to manage group dynamics effectively. For instance, during ice-breaking activities or group discussions led by the research assistant, the music therapist may participate as though they are a group member. This approach helps to foster rapport and strengthen the connection between the facilitators and participants. The same roles and techniques also apply to the research assistant during music activities. Additionally, the research assistant serves as the main point of contact for participants and is responsible for participant follow-up and distribution of reimbursement. The follow-up, limited to the scope of the project, includes administrative liaison (eg, responding to participant inquiries, delivering materials, arranging logistics) and crisis intervention. Crisis intervention involves providing appropriate community crisis support resources and information and making an informed decision regarding the participant’s eligibility to continue with the group intervention.

To enhance project fidelity, the English manual from the original program was revised and translated into Chinese. The music selections from the original program were also adapted by the music therapist to better suit the local context. The incorporated music in this project is intended to produce equivalent therapeutic effects while maintaining consistency in music type with the original selections. For instance, Shawn Mendes’ *A Little Too Much* [50] from the original program was replaced with Eason Chan’s *Today* [51], which is more culturally relevant and relatable for local youth.

The manuals will be printed and distributed to participants and facilitators before the sessions. In cases where distributing hard copies is not feasible, an electronic version will be provided instead. To enhance readability and engagement during session presentations, PowerPoint (Microsoft Corporation) slides aligned with the manual content will also be used.

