### Contingency Plan

Based on prior trials of Tuned In, we expect a high retention rate among youth [6]. However, some attrition may occur among adolescents [25]. Even with that attrition rate, we anticipate retaining at least 30 adolescents at the postintervention stage, providing sufficient data from this pilot study to inform future large-scale trials. In the event of significant challenges in recruiting adolescents, our backup plan is to recruit additional youth from the university community for this trial.

Because of the online mode of intervention, the study design minimizes potential disruptions arising from any local changes in the COVID-19 pandemic situation. If difficulties or delays in participant recruitment arise, we will place advertisements on social media as an additional recruitment channel.

Considering the risk of potential emotional disturbances, a page listing several 24-hour community crisis support hotlines has been incorporated into the manual to provide participants in need with an additional channel to external resources. Alongside the distribution of these resources, the research assistant will also give instructions on how to use them during the group contracting phase and explicitly encourage participants to seek help and notify the research assistant immediately if they experience emotional distress during the session.

In situations where psychological distress is identified either by a facilitator or self-reported by a participant, the research assistant will separate the individual from the rest of the group, while the music therapist continues to lead the remaining activities. The research assistant will provide immediate emotional support and conduct a timely risk assessment, and the principal investigator will be informed of the situation. Based on the participant’s condition, appropriate referrals will be made as necessary.

The research assistant will follow up with individuals who disclose intentions or actions related to self-harm, suicide, harm to others, or breaches of the law, and will discuss with them the appropriateness of continuing in the project or the available options for discontinuation.

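### The post score is scheduled at the last session and the pre-post ANOVA cannot use anyone without one, so loss tied to deterioration in the intervention arm could favour the intervention

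*Protocol article*

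**What the plan says.** - **Analysis.** Under Data Analysis: "For the main outcome evaluation measures, mixed measures ANOVAs will be performed". The factors are group (two levels) and time (pre and post).
- **Collection of the post score.** Under Description of the Intervention: "By the end of the last session, participants will be invited to complete the postquestionnaire". Additional Measure puts the satisfaction ratings and open questions in the same survey and places the open questions at the close of the final session. Study Design sets the control arm's second assessment after the waiting period. Outcome Measures says the outcome scales are run on Qualtrics.
- **Contact during the comparison window.** The waitlist arm gets its sessions only after the experimental group has had its final session and filled in its postquestionnaire.
- **Distress and continuation.** Material and Personnel Preparation includes in crisis intervention a decision on a participant's "eligibility to continue with the group intervention". Under Contingency Plan, after disclosures of self-harm, suicide, harm to others or law-breaking, the research assistant discusses "the appropriateness of continuing in the project or the available options for discontinuation".
- **Expected loss.** Under Sample Size Calculation, "some dropout is expected after the intervention has commenced", estimated at 15%, with no split by arm or reason.

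**The concern.** With two time points, the group × time interaction is a comparison of mean change scores, so a missing post score removes the participant from the test. As written, the post score is sought when the last session ends, and someone who has left the group by then may not be asked. The route by which facilitators notice distress and discuss continuation runs through weekly sessions that only the intervention arm has during the comparison. A deteriorating intervention participant may therefore go missing while a similar control stays in the data.

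Removing poor outcomes from one arm improves that arm's mean without any treatment effect. The primary comparison on the DERS and the secondary comparisons are exposed to this. The satisfaction ratings, which sit in the same survey, would come only from those still present at the end.

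**Working it through.** **1. The plan's own sample size.** Inputs from Sample Size Calculation are partial η² = 0.076, α = 0.05 and 98 participants. Power is not stated, so 80% is assumed, with a two-sided test and equal allocation.
- f = √(0.076/0.924) = 0.287, and d = 2f = 0.574 in SD of change.
- Noncentral F with 1 and N − 2 df and λ = N·f²: power is 0.794 at N = 96 and 0.803 at N = 98. The figure of 98 is reproduced.
- About 50 + 65 = 115 are to be randomised, and 115 × 0.85 = 97.75. The arithmetic fits a plan in which the 15% are lost to analysis. This is an inference, since the article attaches the margin to dropouts before the intervention begins.

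**2. Shift in the null contrast.** Assumptions, none of them in the article: higher scores are worse, pre and post scores have equal SD, the correlation ρ is 0.6, there are 57 per arm and no true effect. A share q of the intervention arm is lost, made up of exactly its worst scorers, and no controls are lost.
- The mean of a standard normal variable after its top share q is cut off falls by s = φ(c)/(1 − q), with c the 1 − q quantile. s = 0.049 at q = 2% and 0.195 at q = 10%.
- If loss follows the post score, the retained baseline mean also falls, by ρs. The shift in change is (1 − ρ)s = 0.4s.
- If loss follows the change score, SD of change = √(2(1 − 0.6)) = 0.894 raw SD, and the shift is 0.894s.

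| Lost from intervention arm | Loss by post score | Loss by change score |
|---|---|---|
| 2% (about 1 of 57) | 0.4 × 0.049 = 0.02 raw SD | 0.894 × 0.049 = 0.04 raw SD |
| 10% (about 6 of 57) | 0.4 × 0.195 = 0.08 raw SD | 0.894 × 0.195 = 0.17 raw SD |

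For scale, the planning effect is 0.574 × 0.894 = 0.51 raw SD. The 10% row is therefore 0.08/0.51 ≈ 15% to 0.17/0.51 ≈ 34% of it, and the 2% row about 4% to 9%.

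**3. Type I error.** Simulation of the same setting (6,000 trials per cell, nominal 5%) gives 5.2% and 5.9% at 2% loss, and 7.7% and 19.4% at 10% loss, for loss by post score and by change respectively.

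**4. Whether a different model repairs it.** In the same simulations a baseline-adjusted analysis, which approximates a likelihood-based mixed model with a common baseline, was also run. At 10% loss by post score its shift is 0.13 raw SD, against 0.08 for the change-score ANOVA, which is worse. At 10% loss by change it is about 0.15 against 0.18 simulated for the ANOVA, which is only slightly better. Neither model corrects loss that depends on the unseen post score.

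**The case against.** A reader might infer that the plan removes distressed participants from the intervention arm alone and analyses completers by rule. The text does not support that reading.

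- No sentence restricts the ANOVA to completers, and a fuller protocol or SAP may deal with missing data. That silence is not the point here. What stands is that the named test cannot use a missing post score and that the article schedules collection at the last session. Later imputation does not recover a score that was lost because of its own value.
- Leavers are not barred from the survey. It is online, participants are reachable by WhatsApp, and the HK $200 is paid for completing both questionnaires, not for attendance. This makes loss less likely, but the article does not say that leavers will be asked.
- The Contingency Plan describes a discussion after serious disclosures, not automatic removal, and severe symptoms are excluded at entry. Removals may well be rare.
- Controls can also disclose to the research assistant, who is the main contact for participants. Selective loss among controls would offset the bias, so the net direction is not fixed.
- Nothing in the article supports a one-arm loss of any particular size. The retention of at least 30 adolescents is a floor over both arms, not a planned loss of 40%. Perfect selection of the worst scorers is an upper bound, because a disclosure of self-harm does not rank people on the DERS.

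These points limit the size and the certainty. They do not remove the gap in collection.

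**Conclusion.** The point holds as a possibility that follows from the stated schedule, not as a demonstrated bias. The weak place is the collection of post scores. The choice of ANOVA is secondary: with post scores from everyone randomised, its interaction test is unbiased.

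Under one-arm, worst-scorer loss with ρ = 0.6 and 57 per arm, the null contrast moves by about 0.02–0.04 raw SD at 2% loss, with type I error about 5–6%. At 10% loss it moves by 0.08–0.17 raw SD, with type I error about 7–20%. The first is negligible and the second would matter. The article gives no figure that decides between them, and less perfect selection or matching loss among controls would shrink both. The correction is cheap enough to be worth making without knowing the rate.

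**What to change.** - **Collection.** Amend Description of the Intervention and Additional Measure so that the Qualtrics post survey goes to every randomised participant at the post time point (end of week 4, or end of the waiting period), regardless of attendance or discontinuation. Send the satisfaction items to anyone who attended at least one session.
- **Analysis.** Analyse all participants in the arm assigned. Report loss and its reasons by arm; the dropout rate is already to be recorded as a feasibility indicator. For post scores still missing, add a delta-adjusted sensitivity analysis in which missing intervention-arm scores are worse by stated amounts.
- **Not a remedy by itself.** A likelihood-based mixed model should not be presented as curing this loss.

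The cost is wording, survey links to people who have stopped attending, slightly more follow-up effort and possibly a smaller estimate. The bias is removed only to the extent that people respond. If collection has already ended, loss by arm and the sensitivity analysis can still be reported. The crisis and continuation procedures are untouched.
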